## 14. STATISTICAL ANALYSIS

### 14.1 Basic statistical procedure

Given the reasonably large sample size employing parametrical methods assuming a Gaussian distribution will be appropriate allowing for parametrical tests. If necessary, logarithmic transformations of skewed parameters are performed, e.g. for number of illness days.

The first step in the analysis will be a crude comparison between the two formula groups 1 and 2 testing the group effect (different formula) for

- quantitative variables by analysis of (co-)variance (ANOVA/ANCOVA)
- qualitative variables by Fisher exact test / Chi-test
- time-related variables (e.g. "time to infection") by percental frequency curves according to Kaplan-Meier functions / Mantel-Cox log-rank test

One example is an analysis of variance with two groups (T-test) with the number of febrile episodes per child as the dependent variable and type of supplementation as a categorical independent variable. Another example is a Kaplan-Meier curve / Mantel-Cox log-rank test of the percentage of infants without infection throughout the study.

[figure not shown]

The second step is a series of univariate analyses to identify confounders by testing the possible influence of characteristics of the infants on the outcome parameters (to be expressed as odds ratio (OR) and 95% confidence intervals (CI)). Variables considered as potential confounders are, e.g., gender, birth weight, number of siblings, attendance to daycare, smoking in household, duration of breastfeeding, etc.

The third step is a multivariate analysis to identify interaction variables, i.e. confounders which interact with exposure (feeding active formula or placebo).

The final analysis is aiming at simultaneous control of possible confounders and interaction variables by multiple regression analysis with stepwise variable selection to achieve a model that is parsimonious (has only few variables) but maximizes the proportion of the explained variance across study groups. Stepwise procedure:

- baseline model including exposure and core variables,
- stepwise introduction of two-way interaction terms involving exposure (p value to enter 0.05),
- elimination of variables not involved in significant interactions in the multiple regression model (change in exposure odds ratio < 5%).

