## 10.5 Number of subjects and study power

Starting with 500 formula infants per group, it is assumed that about 35% will be lost for the per-protocol-analysis due to continuation of breastfeeding beyond the second month of life and further about 15% due to different dropout / withdrawal reasons so that 250 infants per formula group fully completing the study should be achieved.

With those 250 formula infants per group completing the study without violation of the protocol, a reduction of the mean number of febrile episodes by 1 which is considered as clinically relevant reduction (from 4.5 to 3.5, SD 3.5 episodes), compared to placebo can be proven with 93% power in an one-sided unpaired t-test or 89% in a two-sided unpaired t-test.

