## 14.3 Comparative analyses

If the data distribution of the respective parameter does not indicate a major deviation from Gaussian normal distribution, parametric tests will be used for group comparisons.

If the study hypothesis does not explicitly define the direction of group differences (e.g. parameter mean of group 1 significantly *less* (or *more*) ... than parameter mean of group 2) all tests will be performed two-sided.

Biometrical significance of group differences will be accepted if the null hypothesis (no group difference) is denied with an alpha-error of 0.05 (5%).

In case we assume equivalency for data, e.g. data on growth, acceptance, and tolerance in all groups), no correction for multiple comparisons by adjusting the level of alpha-error will be performed for those data in order to maintain the sensitivity of the tests to be used. However, for data assumed to be different between the groups, e.g. faecal flora, statistical analyses will be corrected for multiple comparisons (groups, time points) by adjusting the level of alpha-error according to accepted procedures, e.g. Bonfferoni.

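### Section 14.1 calls a stepwise regression with an uncontrolled search for treatment interactions the final analysis, and nothing says whether it or the powered t-test decides the primary hypothesis

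*Protocol*

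**What the plan says.** Protocol section 14.1 describes a sequence:

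1. A crude comparison of the two formula groups. One example given is a t-test on febrile episodes per child.
2. Univariate analyses to find confounders. The candidates are introduced as examples: gender, birth weight, number of siblings, "attendance to daycare, smoking in household, duration of breastfeeding, etc".
3. A multivariate search for confounders that interact with the formula.
4. A final analysis by multiple regression with stepwise selection. It starts from exposure and unnamed core variables and continues with "stepwise introduction of two-way interaction terms involving exposure (p value to enter 0.05"). The last step is "elimination of variables not involved in significant interactions in the multiple regression model (change in exposure odds ratio < 5"%).

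Section 10.4 adds that potential confounders other than centre will be checked and adjusted for in the final data analysis. Section 10.1 says that breastfeeding before and after study entry will be examined as a possible confounder in the formula groups.

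The power statement in section 10.5 concerns the unadjusted test. "With those 250 formula infants per group completing the study without violation of the protocol", the planned reduction ("from 4.5 to 3.5, SD 3.5 episodes") "can be proven with 93% power in an one-sided unpaired t-test or 89% in a two-sided unpaired t-test". Section 14.3 sets alpha at 0.05 and describes its multiplicity correction in terms of groups and time points.

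**The concern.** The analysis that carries the name final is chosen by looking at the outcome. Each candidate interaction gets its own 5% chance to enter, the list of candidates is open, and no correction covers the search. Once an interaction is in the model under 0/1 coding, the exposure coefficient describes the infants coded zero on that covariate, not the trial population.

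Two named candidates are also doubtful as adjustment variables. Infants enter, and are randomised, by 8 weeks of age (sections 8 and 10.4). Later breastfeeding and most day-care attendance therefore follow allocation, and adjusting for something that the formula could influence can bias a randomised comparison.

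The trial could thus end with a crude and a stepwise answer that disagree, and no rule for choosing between them. It could also report a subgroup-specific benefit of a formula that does nothing.

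**Working it through.** **Inputs.** From the protocol: alpha 0.05 (14.3); 250 per group, difference 1.0 episode, SD 3.5 (10.5); entry at p<0.05, removal at a change below 5%, six named candidates (14.1). My assumptions: the screening threshold (p<0.05), the distribution, coding and prognostic strength of the covariates, and a change in the regression coefficient standing in for a change in odds ratio.

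**1. The plan's own power.** Standardised difference = 1 / (3.5 × √(2/250)) = 3.194.
- Two-sided: Φ(3.194 − 1.960) = 89.1%, against 89% stated.
- One-sided: Φ(3.194 − 1.645) = 93.9%, against 93% stated.

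The stated power is reproduced to within a point, and it belongs to the crude t-test.

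**2. Interaction search, all candidates tested.** With k independent tests, P(at least one false interaction) = 1 − 0.95^k.
- k = 6: 26.5%
- k = 10: 40.1%
- k = 12: 46.0%

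**3. Interaction search after a univariate screen.** A covariate unrelated to outcome passes the screen and then the interaction test with probability of about 0.05 × 0.05 = 0.0025. A strongly prognostic one always passes the screen. With m prognostic covariates among k, P ≈ 1 − 0.95^m × 0.9975^(k−m).
- k = 6, m = 0: 1 − 0.9975^6 = 1.5%
- k = 6, m = 3: 1 − 0.8574 × 0.9925 = 14.9%
- k = 6, m = 6: 26.5%
- k = 12, m = 6: 1 − 0.7351 × 0.9851 = 27.6%

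Weaker prognostic factors pass the screen less often; simulated rates were then about 19-21% for 6 of 6 or 6 of 12.

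**4. Null simulation of the written procedure.** Settings: 250 per group, over-dispersed counts with mean about 4.5 and SD about 3.7, no treatment effect, all covariates mildly prognostic, 4,000 runs per setting with six covariates.

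| Six covariates | Crude test p<0.05 | Any interaction enters | Exposure coefficient p<0.05 |
|---|---|---|---|
| Centred, no screen | 4.6% | 29.1% | 4.5% |
| Centred, screened | 4.9% | 25.3% | 4.7% |
| Uncentred, no screen | 5.2% | 29.5% | 7.3% |
| Uncentred, screened | 4.8% | 25.4% | 6.5% |

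With 12 covariates and a screen, an interaction entered in 28-30% of runs; unscreened lists of 12 gave about 45%. With six unscreened, independent 0/1 covariates, the exposure coefficient reached p<0.05 in about 14% of trials.

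**5. The removal rule in isolation.** With interactions switched off, the 5% change-in-estimate rule gave p<0.05 in 4.5% of null trials, so it does not inflate the error.

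**The case against.** The best reply is that a valid test is already in the plan. The crude t-test is the first step, it is illustrated with the primary outcome, it is the test that was powered, and it holds 5%. Final may only mean last in a sequence. That is a fair reading, but it is nowhere stated, and section 10.4 also places adjustment in the final data analysis. The missing hierarchy remains.

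Several stronger readings are tempting and are not supported:

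- **That false interactions would appear in about half of trials or more.** With all of a list of 25 factors, about the length of section 6.4.1, 1 − 0.95^25 = 72.3%. That skips the univariate step that section 14.1 orders. With an assumed 5% screen the rate is far lower unless several covariates are prognostic.
- **That the treatment effect itself is tested at several times 5%.** The 14% figure needs unscreened 0/1 covariates. Centred, the coefficient stays near 5%.
- **That keeping covariates by how far they move the estimate inflates error.** It did not (step 5). Its fault is that the model is not fixed in advance.
- **That the odds-ratio criterion is wrong throughout.** Section 14.1 also covers qualitative outcomes and the synopsis lists logistic regression, where it can apply. It cannot be applied to a linear regression of the episode count.
- **That breastfeeding duration is wholly post-randomisation.** Some precedes entry, particularly in per-protocol infants, who reach full formula feeding by 2 months. The objection is stronger for the intention-to-treat set and for day-care.

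**Conclusion.** The point holds in a limited form. The protocol does not say which analysis decides the primary hypothesis, and the one it calls final contains an interaction search without multiplicity control. This is a rule that the protocol itself sets, with its own entry and removal thresholds, not a detail left for a later analysis plan.

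Its size under the null is about 25-30% of trials with at least one false treatment interaction if the six named variables are all tested. With a screen it runs from about 1-2% (none prognostic) to roughly 20-30% (several prognostic), and about 45% for 12 unscreened candidates. For six covariates the exposure coefficient's own error rate is about 5% centred and about 7-14% with 0/1 coding. These figures rest on independent covariates and on the assumed screening threshold. The interaction rate counts as misleading only if a selected interaction would be reported as a finding, which nothing in section 14.1 prevents. A reader should not infer that the trial has no valid test; it has one, without the status of primary.

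**What to change.** In section 14.1, name one primary analysis of the number of febrile episodes. Either of these would do:

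- the two-group comparison on which section 10.5 is powered; or
- one model with treatment, centre and a short, fixed list of pre-randomisation covariates, with no variable selection and no interaction terms.

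Keep variables that arise after randomisation, such as later breastfeeding and day-care attendance, out of it. Label the confounder screening, the interaction search and the stepwise model exploratory; they need not be deleted. Confine the odds-ratio criterion to outcomes that yield an odds ratio. Bring the adjustment sentence in section 10.4 into line.

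The cost is wording only. If the t-test is named, its power stays at 89.1% two-sided or 93.9% one-sided under the plan's assumptions. The downside is that covariates found to be predictive only in the data are not used in the primary model.

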## 14.2 Descriptive analyses

For all *interval data* obtained at any date of measurement (e.g. quantitative data on faecal flora or anthropometric data) descriptive statistics will be computed for each feeding group including graphical analyses (scattergrams, single development curves, boxplots). If necessary, logarithmic transformation of data will be performed for homogenisation of variances (e.g. bacterial counts).

For *ordinal and nominal data* obtained at any date of measurement (qualitative data on faecal flora, acceptance and tolerance of feedings, single observations) percental frequencies will be calculated for each feeding group and visualised as bar and/or pie charts.

For time-related parameters (calculated data, e.g. time until occurrence of ... or time until ... was reached) graphical analyses will be performed for each feeding group by means of percental frequency curves according to Kaplan-Meier-functions.

## 14.3 Comparative analyses

If the data distribution of the respective parameter does not indicate a major deviation from Gaussian normal distribution, parametric tests will be used for group comparisons.

If the study hypothesis does not explicitly define the direction of group differences (e.g. parameter mean of group 1 significantly *less* (or *more*) ... than parameter mean of group 2) all tests will be performed two-sided.

Biometrical significance of group differences will be accepted if the null hypothesis (no group difference) is denied with an alpha-error of 0.05 (5%).

In case we assume equivalency for data, e.g. data on growth, acceptance, and tolerance in all groups), no correction for multiple comparisons by adjusting the level of alpha-error will be performed for those data in order to maintain the sensitivity of the tests to be used. However, for data assumed to be different between the groups, e.g. faecal flora, statistical analyses will be corrected for multiple comparisons (groups, time points) by adjusting the level of alpha-error according to accepted procedures, e.g. Bonfferoni.

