#### **5. WORKING HYPOTHESIS**

It is hypothesised that dietary intervention with a formula (IF/FOF) supplemented with a mixture of immunomodulating neutral and acidic oligosaccharides will significantly reduce the incidence of febrile infectious diseases in healthy term born infants during the first year of life when compared to control infants receiving the placebo formula as indicated by

- primary parameter: number of febrile episodes (peak rectal temperature at least 38.5 °C) and
- secondary parameter: symptoms of infection (cough, wheeze, runny nose, vomiting, diarrhoea etc.) and their duration.

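### The sidedness of the primary test is not fixed, and the plan's own rule allows a one-sided test at an unadjusted 5%

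*Protocol*

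**What the plan says.** Four places in the protocol bear on this.

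- **Section 14.3 (Comparative analyses)** ties sidedness to the wording of the hypothesis: "If the study hypothesis does not explicitly define the direction of group differences", then "all tests will be performed two-sided". It does not say what happens when a direction is defined. It sets the significance criterion at an alpha-error of 0.05, with no separate level for one-sided tests.
- **Section 5 (Working hypothesis)** defines a direction. The active formula "will significantly reduce the incidence of febrile infectious diseases in healthy term born infants" compared with the control formula. The count of febrile episodes is named as the primary parameter for that hypothesis, with symptoms of infection and their duration as the secondary one.
- **Section 10.5 (Number of subjects and study power)** says that a one-episode reduction ("from 4.5 to 3.5, SD 3.5 episodes") "can be proven with 93% power in an one-sided unpaired t-test or 89% in a two-sided unpaired t-test". Its power table has one-sided and two-sided columns, all at alpha 0.05.
- **Section 14.1 (Basic statistical procedure)** gives a two-group analysis of variance, equated with a t-test, as one example of how febrile episodes per child might be compared. It does not state sidedness.

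**The concern.** A confirmatory trial should settle before the data are seen what counts as success on the primary parameter. Here the rule in 14.3 has a gap exactly where the primary hypothesis sits: two-sided testing is required for undirected hypotheses, and the primary hypothesis is directed. Section 10.5 could have closed the gap but gives both powers.

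Two things are at stake. If the one-sided route is taken at the stated 0.05, the chance of wrongly declaring a benefit is 5%, twice the 2.5% that a two-sided 5% test allows in that direction. And because the choice is open, a borderline favourable result can be called either a success or a failure without breaching the protocol.

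**Working it through.** **Inputs.** From 10.5: 250 infants per group, means 4.5 and 3.5 (difference 1), SD 3.5, alpha 0.05, unpaired t-test. Degrees of freedom = 2 × 250 − 2 = 498.

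**Step 1: reproduce the plan's power.**

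- Standard error of the difference: SE = SD × √(2/n) = 3.5 × √(2/250) = 0.313.
- Standardised difference: 1 / 0.313 = 3.19.
- One-sided 0.05, normal approximation: Φ(3.19 − 1.645) = 93.9%. The noncentral t distribution also gives 93.9%. The protocol states 93%.
- Two-sided 0.05, normal approximation: Φ(3.19 − 1.96) = 89.1%. The noncentral t distribution gives 89.0%. The protocol states 89%.

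Both figures reproduce to within one point. The one-sided figure fits only an unreduced one-sided alpha of 0.05: at one-sided 0.025 the power is 89.0%, the same as two-sided 0.05. So the one-sided option in 10.5 is a 5% test.

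**Step 2: error in the direction of benefit.** A one-sided 0.05 test puts all 5% there. A two-sided 0.05 test puts 0.05 / 2 = 2.5% there. The ratio is 5.0 / 2.5 = 2, whatever the sample size or SD.

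**Step 3: smallest significant reduction** (critical t × SE).

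| Test | Critical t (498 df) | Smallest significant reduction |
|---|---|---|
| One-sided 0.05 | 1.648 | 1.648 × 0.313 = 0.516, about 0.52 episodes |
| Two-sided 0.05 | 1.965 | 1.965 × 0.313 = 0.615, about 0.62 episodes |

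**Step 4: how often the choice decides the result.** The disputed zone is a one-sided p between 0.025 and 0.05.

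- With no true effect, the result falls there with probability 5.0% − 2.5% = 2.5%.
- With the planned one-episode reduction, the probability is 93.9% − 89.0% = 4.9%.

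**The case against.** The strongest defence is that 14.3 never prescribes a one-sided test. It says when tests must be two-sided and is silent otherwise. The methods named elsewhere lean towards two-sided testing: the analysis of variance in 14.1 has an F-test with no direction, and the chi-square, Kruskal-Wallis and log-rank tests are usually reported two-sided. A one-sided 5% test fixed in advance is also legitimate and controls its stated error. Finally, sidedness is often settled in a statistical analysis plan, which is not shown here.

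Much of this stands, and it limits the point. A reader might infer that one-sided testing is the default for the primary parameter; the text allows it only by implication. But 14.1 offers its analysis as an example and equates it with a t-test, which can be run one-sided, so it does not close the gap. Nor is the protocol merely silent: it states a rule, that rule releases the primary test from the two-sided requirement, and 10.5 then advertises both powers.

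Two further inferences go too far.

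- *That the symptom outcomes would be tested one-sided at a full 5%.* Section 14.3 also calls for a multiplicity adjustment for data expected to differ between groups. Its bracket mentions only groups and time points, but the symptom outcomes may fall under it.
- *That harm would go unassessed.* Section 13.6 judges safety partly against the control group and records unanticipated adverse events, and an excess of fever would show in the estimated difference. What a one-sided test lacks is only a formal test in that direction.

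**Conclusion.** The point holds as a defect in the decision rule: the sidedness of the primary test is left open, and a one-sided test at an unadjusted 5% is within the rule as written. The consequence is a benefit-direction error of 5% or 2.5%, and a significance threshold of about 0.52 or about 0.62 episodes. Only results in the narrow zone between the two are affected.

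The doubling of the error needs no assumption beyond alpha 0.05, and it is measured against the customary two-sided 5% test. The two thresholds rest on the protocol's 250 per-protocol infants per group, SD 3.5 and a t-test on the count; a larger analysis set or a different SD would shift both.

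The quoted power figures are not wrong, and the trial is not underpowered on its own inputs by this point. The change should be made because it removes a possible choice after the data are seen at almost no cost.

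**What to change.** - In 14.3, state that the primary comparison of febrile episodes, and other hypothesis tests of a difference, are two-sided at 0.05, and that the primary difference is reported with a 95% confidence interval. Delete the exception that depends on whether the hypothesis has a direction. The directional wording in section 5 can stay as the scientific expectation.
- In 10.5, keep only the two-sided power of 89% for 250 per group, difference 1, SD 3.5, and drop the one-sided figure and the one-sided table columns.

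The cost is a few sentences by amendment, and the quoted power falls from 93% to 89%. The sample size stays as it is, because the protocol already reports 89% two-sided power at 250 per group.

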Safety is also defined as absence of *unanticipated*\* adverse effects compared to baseline (pre-treatment) or “normal” conditions as indicated by the control group. All *unanticipated* adverse events encountered during the study after treatment has started, whether considered related to treatment or not, will be reported on the subject’s record: intensity, relationship to test substance, action taken regarding test substance, and outcome to date (see Unanticipated Adverse Event Report Form the annex). Such preliminary reports will be followed by detailed descriptions when available.

*Unanticipated serious*\* adverse events thought to be associated with the study feeding will be reported to NUMICO Research Germany within 24 hours (Telefax [name], Telephone [name] [name]).

NUMICO Research has effected an insurance in connection with this study which meets the requirements as established, e.g., by the “De Nederlandse Wet Medisch Wetenschappelijk Onderzoek met Mensen”.

---

\* *Unanticipated adverse events* are defined as any event, the specificity or severity of which is not consistent with those known from the risk information in the consent form (e.g. for blood samplings) or are reasonably expected to accompany the natural history and progression of the subjects’ condition throughout the study.

*Serious adverse events* are generally defined as events that result in any of the following outcomes: death, a life threatening experience; inpatient hospitalisation or prolongation of existing hospitalisation; a persistent or significant disability/incapacity; or a congenital anomaly/birth defect. In addition, events that may not result in death, be life-threatening, or require hospitalisation may be considered serious when, based upon appropriate medical judgement, they may jeopardise the subject and may require medical or surgical intervention to prevent one of the outcomes listed above.

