### **14.3.1 Interval data**

Inter-group comparisons will be performed for all interval data at any measurement point by using the analysis of variance (ANOVA) / T-test (if necessary to perform non-parametric tests -> Kruskal-Wallis test / Wilcoxon-Mann-Whitney U-test). In case of significance of the multiple group comparison, single group comparisons will be performed as post-hoc tests according to Fisher (if necessary to perform non-parametric tests -> Wilcoxon-Mann-Whitney-U-test).

For baseline adjustment, comparisons will be calculated not only using the raw data but also data differences (e.g. data at examination day 2 and 3 minus data at examination day 1) to account for individual variances.

Whenever needed, logarithmic transformation of data will be performed for homogenisation of variances prior to statistical analysis.

Within-group comparisons (e.g. examination day 3 versus day 1) will be conducted using the paired T-test (if necessary to perform non-parametric tests -> Wilcoxon-signed rank test).

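### Growth, acceptance and tolerance are assumed equivalent, but the plan offers only difference tests at 5%, with no margin or confidence interval that could show equivalence

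*Protocol*

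**What the plan says.** Section 14.3 divides the variables into two kinds. Those expected to differ, such as faecal flora, get an alpha correction. For the others it says: "In case we assume equivalency for data, e.g. data on growth, acceptance, and tolerance in all groups), no correction for multiple comparisons" will be made, "in order to maintain the sensitivity of the tests to be used". Significance is declared when the null hypothesis of no group difference is rejected at 5%. Where the study hypothesis sets no direction, "all tests will be performed two-sided".

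The tests named are ANOVA or t-test, with rank tests as fallback, for interval data (14.3.1); Kruskal-Wallis or U-test for ordinal data such as regurgitation and vomiting (14.3.2); and chi-square for nominal tolerance data (14.3.3). Section 14.1 compares "qualitative variables by Fisher exact test" or chi-square. All are tests of a difference. Confidence intervals appear only in 14.1, for odds ratios in the confounder search.

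Section 13.6 describes safety as the absence of unanticipated "adverse effects compared to baseline (pre-treatment) or" the normal state shown by controls. Section 10.5 calculates power for febrile episodes only.

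**The concern.** A test of no difference can give evidence of a difference. If it is not significant, the groups may be alike or the data may be too few, and the p-value does not tell these apart. Leaving alpha uncorrected makes the tests a little more likely to flag a harm, which is the right direction. It does not supply a criterion for equivalence.

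The plan therefore assumes equivalence for growth, acceptance and tolerance and gives no way to show it. At stake is what may be said about a product fed to healthy infants up to one year of age. The assumption is not a formality for growth: in appendix 21.1 the active and control follow-on formulas also differ in protein (1.4 against 1.8 g per 100 ml) and energy (67 against 70 kcal), although that table is marked as not yet definitive.

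**Working it through.** **1. The plan's own figure.** Section 10.5: 250 per group, difference 1 episode, SD 3.5. The standardised difference is 1 / (3.5 × √(2/250)) = 3.194. Two-sided power = Φ(3.194 − 1.960) = 89%; one-sided = Φ(3.194 − 1.645) = 94%. The plan states 89% and 93%, so the figure reproduces. No such figure exists for growth, tolerance or adverse events.

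**2. Inputs.** Alpha 0.05, two-sided (14.3). Per arm: 500 randomised and 250 per-protocol completers (10.5). Control event rate: not given, so assumed from 0.5% to 10% and doubled in the active arm.

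**3. Chance of missing a doubling.** Approximate power is Φ[(d√n − 1.96√(2p̄q̄)) / √(p₁q₁ + p₂q₂)], where d = p₂ − p₁, p̄ is the mean of the two rates, and q = 1 − p. For 2% to 4% with n = 500: d√n = 0.447; 1.96 × √(2 × 0.03 × 0.97) = 0.473; denominator √(0.0196 + 0.0384) = 0.241. Power = Φ(−0.106) = 46%. Enumerating all outcomes gives these miss rates:

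| Control to active | 250, chi-square | 250, Fisher | 500, chi-square | 500, Fisher |
|---|---|---|---|---|
| 0.5% to 1% | 92.3% | 98.7% | 86.8% | 93.2% |
| 1% to 2% | 86.5% | 93.2% | 75.7% | 82.0% |
| 2% to 4% | 74.1% | 82.2% | 53.9% | 60.1% |
| 3% to 6% | 63.5% | 70.4% | 36.5% | 41.7% |
| 4% to 8% | 52.8% | 59.4% | 23.5% | 27.4% |
| 5% to 10% | 42.8% | 48.8% | 14.2% | 16.8% |
| 10% to 20% | 11.3% | 13% (simulated) | 0.6% | 1% (simulated) |

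The miss rate passes one half at a control rate of about 4% with 250 per arm and about 2% with 500, under either test. If 15% of 500 drop out, leaving 425, chi-square misses 59.6% at 2% to 4% and 43.8% at 3% to 6%.

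**4. What equal observed rates would exclude.** The upper 95% limit of the risk ratio is exp[1.96√(2(1 − p)/(np))]. At 2% in both arms it is exp(1.96 × √0.196) = 2.4 with 500 and exp(1.96 × √0.392) = 3.4 with 250. With 10 events in each arm of 500, the Newcombe 95% interval for the risk difference is −1.9 to +1.9 percentage points, so an excess nearly as large as the 2% background rate stays possible.

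**5. Growth.** SD of the z-score assumed to be 1. Half-width of the 90% interval: 1.645 × √(2/250) = 0.147 SD, and 1.645 × √(2/500) = 0.104 SD. If the true difference is zero, the chance that the 90% interval lies inside a margin m is 2Φ(m/√(2/n) − 1.645) − 1:

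| Margin (illustrative) | 250 per arm | 500 per arm |
|---|---|---|
| 0.20 SD | 45% | 87% |
| 0.25 SD | 75% | 98% |
| 0.30 SD | 91% | over 99% |
| 0.50 SD | over 99% | over 99% |

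A margin rule for growth is therefore workable with the planned sample.

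**The case against.** The sentence in 14.3 is a rule on multiplicity. It does not say that a non-significant result will be read as equivalence, and the aim and hypothesis (sections 4 and 5) make no equivalence claim. A reader might infer that the trial will report the supplemented formula as equivalent and free of harm. That would be a prediction about a report, and the protocol does not contain it. What stands is narrower: equivalence is assumed, and the protocol holds no criterion other than the difference test.

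A reader might also infer that absence of adverse effects is to be tested at 5%. Section 13.6 concerns only unanticipated effects, a term it defines narrowly, and it prescribes case recording and reporting. No test is assigned to them; using Fisher or chi-square here extends the general rule for qualitative variables.

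The yes/no calculation does not carry over to regurgitation and vomiting, which are analysed as ordinal data. Low power for rare harms affects any trial of this size. Margins and intervals for safety variables are often left to an analysis plan, and nothing in section 14 forbids them. These points lower the weight of the concern. They do not remove the mismatch between assuming equivalence and naming only tests of difference.

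**Conclusion.** The point holds as an inexpensive improvement to the safety analysis; the primary comparison is unaffected. The protocol's difference tests cannot show the equivalence that it assumes for growth, acceptance and tolerance.

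The size of the problem depends on the variable. Growth is well covered: a difference of 0.25 SD is detected with 80% power at 250 per arm and 0.18 SD at 500, so only a margin is lacking. Common tolerance events are also covered, since a rise from 10% to 20% is rarely missed. The weakness lies in uncommon yes/no events. The broader reading that any doubling of a harm would usually go unnoticed is not supported: with 500 per arm it already fails at an assumed control rate of 3%. The limits of about 2% (500 per arm) and 4% (250 per arm) rest on assumed rates.

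**What to change.** In section 14.3, keep the tests and the uncorrected alpha for these variables, and add that any statement of equivalence rests on the active-minus-control confidence interval in all randomised infants.

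- **Growth z-scores:** equivalence is stated only if the 90% interval (two one-sided 5% tests) lies within a margin that the clinical team names before unblinding.
- **Yes/no tolerance and adverse events:** report the risk difference with its 95% interval and state the excess that is not excluded. Do not conclude equivalence or absence of harm from p > 0.05. Cross-refer to this in 13.6.

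Using all randomised infants matters because section 18 removes dropouts, non-compliers and infants whose feeding regimen is discontinued from the per-protocol set. An infant who stops the formula for intolerance would leave that set.

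The cost is wording and one decision on a margin, with no extra infants, visits or data. The downside is a more modest safety statement for uncommon events.
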